## Study Data Protection

The collection and processing of personal data from participants enrolled in the study will be limited to those data that are necessary to fulfill the objectives of this study. These data must be collected and processed with adequate precautions to ensure confidentiality and compliance with applicable data protection laws and regulations.

An eCRF will be available in REDCap. The eCRF will be completed for all participating patients. This eCRF will include specific pages for inclusion and exclusion criteria, and for reporting each visit. Other specific pages will be dedicated to concomitant treatments and AEs (non-serious and serious). The investigator will review, approve, and validate each completed eCRF; the investigator's signature (validation) serving as attestation of the investigator's responsibility for ensuring that all data entered on the eCRF are complete, accurate and authentic. All data will be processed according to the principles that the new European General Data Protection Regulation (GDPR) imposes, which are in force since 25 May 2018. The STIMULUS Research Group, Vrije Universiteit Brussel, will be responsible for the processing of personal data. The Data Protection officer is [[contact]](mailto:[contact]). The processing of personal data is for scientific research purposes and will happen on the legal basis of consent that can be withdrawn by the patient. All researchers involved in this clinical trial or in research projects that use materials original from this clinical trial are potential recipients of the personal data, as well as staff involved in monitoring and ethical evaluation and people from CA and subcontracted parties that perform analysis on study-related data or materials. It is possible that personal data will be viewed by people who are in countries that do not use the same standards as the EU in terms of legal protection of data. In that case, we guarantee that the conditions of European and Belgian legislation on the protection of personal data will be respected. The study-related documents will be stored for at least 25 years.

## Subject Identification

The participant identification will be treated as confidential and will be filed by the investigator in an identification log. This log is kept at the participating site and shall not be copied. In all reports and communication between the site and the Sponsor the participant shall be identified with a participant study number.

## Insurance

VUB is, as sponsor of the trial, responsible for ensuring appropriate general/product liability insurance and as required in accordance with applicable laws and regulations, country-specific liability insurance coverage for claims made by a trial subjects for injury arising from the subject's participation in the trial.

In accordance with the Belgian law relating to experiments in humans dated May 7, 2004 the sponsor shall be liable, even without fault for any damages incurred by the study participant and linked directly or indirectly to the participation to the study and the sponsor shall provide compensation therefore through its insurance program. Before commencing the study, the sponsor shall enter an insurance contract which covers this liability, and the liability of every individual intervening in the study, irrespective of the nature of the affiliation between the intervening individual, the sponsor and the study participant. Every contractual provision aiming at limiting this liability is considered null and void.

The participating site, the investigator and sponsor shall have and maintain in full force and effect during the term of this Agreement (and following termination or completion of the Study to cover any claims arising from the Study) adequate insurance coverage for: (i) medical professional and/or medical malpractice liability, and (ii) general liability resulting from the study at the participating site required by local law, each such insurance coverage in amounts appropriate to the conduct of the services of the participating site, the investigator and sponsor under this agreement. The participating site and sponsor shall be solely responsible for any deductible or self-insured retention under any such policies.

## Reporting and Dissemination

The data and information collected during this trial will be reported in a publication in a scientific/medical journal. Reporting of trial results will be performed according to local regulations.

For the correct authorship rules we refer to the International Committee of Medical Journal Editors: <https://www.icmje.org/recommendations/browse/roles-and-responsibilities/defining-the-role-of-authors-and-contributors.html>

## Finance and Conflict of Interest Statement

This study is funded by Research Foundation Flanders through the TBM program (project number T000525N). Investigators and study team members will provide the sponsor with sufficient, accurate financial information in accordance with local regulations to allow the sponsor to submit complete and accurate financial certification or disclosure statements to the appropriate regulatory authorities/ethics committee. Any update of information on financial interests should be disclosed during the course of the study.

## Tables and Figures

| What? | Patient comfort *                                                                                                                                                    | QoL *        | Pain Intensity * | Pain interference * | Stress *          | Anxiety * | Self-efficacy * | Burden caregivers * | Patient satisfaction | Tele-monitoring quality** + time | Safety                                                    | Health expenditure *** | Patient preference    |
|-------|----------------------------------------------------------------------------------------------------------------------------------------------------------------------|--------------|------------------|---------------------|-------------------|-----------|-----------------|---------------------|----------------------|----------------------------------|-----------------------------------------------------------|------------------------|-----------------------|
| How?  | GCQ                                                                                                                                                                  | MQOL + EQ-5D | VAS              | PROMIS              | Sarsted t AG & Co | STAI      | GSE             | ZBI                 | Likert-scales        | Likert-scales + time expenditure | Overall safety + environmental safety + sterile procedure | Phone calls            | Multiple choice + DCE |
| When? | At baseline * and after each intrathecal pump refill (** only applicable for refills at home)
***Four weeks after first refill and four weeks after second refill |              |                  |                     |                   |           |                 |                     |                      |                                  |                                                           |                        | After last refill     |
| Who?  | Patient                                                                                                                                                              | Patient      | Patient          | Patient             | Salivary sample   | Patient   | Patient         | Caregiver           | Patient              | Researchers                      | Patient + researchers                                     | Patient                | Patient               |

**Table 1: Overview outcomes.** Abbreviations: GCQ = General Comfort Questionnaire; MQOL = McGill Quality of Life Questionnaire; EQ-5D = EuroQol with five dimensions; VAS = Visual Analogue Scale; PROMIS = Patient-Reported Outcomes Measurement Information System; STAI = State Trait Anxiety Inventory; GSE = General Self-Efficacy; ZBI = Zarit Burden Interview, DCE = Discrete choice experiment.

| Attributes                                                              | Levels                                                                                                                                      |
|-------------------------------------------------------------------------|---------------------------------------------------------------------------------------------------------------------------------------------|
| Travel time + waiting time                                              | 
 
0 minutes
 
45 minutes
 
90 minutes
 
                                         |
| Person who performs the refill                                          | 
 
Always the same person
 
Team of 2 persons (alternating)
 
Always different
 
 |
| Risk of wound infection                                                 | 
 
1 in 100 refills
 
1 in 500 refills
 
1 in 1.000 refills
 
                    |
| Additional required amount that you should have to pay (non-reimbursed) | 
 
0 euro
 
40 euros
 
70 euros
 
                                                |

**Table 2: Varying levels of different attributes.**

|                                                                                | Scenario A (refill at home)                               | Scenario B (refill at the hospital)                         |
|--------------------------------------------------------------------------------|-----------------------------------------------------------|-------------------------------------------------------------|
| Travel time + waiting time                                              | There is no extra travel time or waiting time             | Your total travel and waiting time is 90 minutes.           |
| Person who performs the refill                                          | Every refill is performed by a different person           | Every refill is performed by the same person                |
| Risk of wound infection                                                 | The risk of a wound infection for you is 1 in 500 refills | The risk of a wound infection for you is 1 in 1.000 refills |
| Additional required amount that you should have to pay (non-reimbursed) | The cost for you is 40 euros.                             | The cost for you is 0 euros                                 |

*Table 3: Example of a choice set “Which scenario do you prefer for your refill procedure?”.*

[figure not shown]

*Fig. 1: Study flowchart. Created in <https://BioRender.com>*

[figure not shown]

**Fig. 2: Overview home visit.** Created in <https://BioRender.com>

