### Inclusion Criteria

- Adult patients, 18 years or older
- Actively receiving IDD
- Stable medication dosage for at least 3 months
- Dutch, French or English speaking

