#### Willingness-to-pay (WTP)

In addition to the cost-utility analysis, where QoL and life-years play a prominent role, a DCE will be conducted to estimate the WTP for pump refills at home. This preference elicitation method will help inform future reimbursement policy decisions by capturing the broader value that society places on the intervention (85).

A DCE is based on the idea that people's choices between different options depend on specific characteristics, or attributes, of those options. By systematically varying these attributes across scenarios and asking participants to choose between them, it is possible to estimate how much each attribute influences decision-making. This method will allow reverse engineer choice to quantify the impact of changes in attribute levels on choice. The results will complement the health economic evaluation by providing insight into preferences and perceived value from a societal perspective (86).

A literature review has been conducted to obtain the variables that represent the patient-centered values relevant to DCE (87-97). The following attributes will be used:

- Travel time and waiting time
- Person who performs the refill procedure
- Risk of wound infection
- Additional required amount that you should have to pay (non-reimbursed)

Each attribute is divided into multiple levels (Table 2, section 15). By combining different attributes and their corresponding levels, various scenarios can be created. These attributes will be presented in a choice set consisting of two scenarios (A and B), each representing different combinations of attribute levels (Table 2, section 15). Patients will be asked to choose between the two scenarios presented. During the study, patients will be asked to complete the DCE after the fourth refill. An example of such a choice set is shown in Table 3 (section 15).

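### The discrete choice experiment shows infection risk with changing denominators, which hides an 8:1 difference between the risk steps and could bias the weight on infection risk

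*Protocol*

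**What the plan says.** The willingness-to-pay part of protocol section 10.4.3 states that "a DCE will be conducted to estimate the WTP for pump refills at home", to help inform reimbursement policy. The choices are to be used to "quantify the impact of changes in attribute levels on choice". Four attributes are listed; wound infection is the only harm among them.

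Table 2 in section 15 gives the infection attribute three levels: "1 in 100 refills", "1 in 500 refills" and "1 in 1.000 refills". Table 3 shows an example choice set as a patient would read it. The home scenario reads "The risk of a wound infection for you is 1 in 500 refills" and the hospital scenario "The risk of a wound infection for you is 1 in 1.000 refills". Neither table gives a percentage or a common denominator.

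The DCE is completed once, after the fourth refill (sections 6.3 and 10.4.3). Eligible patients are "Dutch, French or English speaking" (section 8.2).

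**The concern.** A respondent has to compare two risks whose numerator is fixed and whose denominator moves. The numbers that catch the eye are 100, 500 and 1.000. They suggest two steps of similar size, and the larger number means the smaller risk. The risks behind them are spaced very differently.

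A respondent who works from the visible numbers would treat the change from 500 to 1,000 as at least as important as the change from 100 to 500. The DCE would then record too large a weight for the small risk step, relative to the large one. Infection risk is traded against travel time, continuity of the person refilling and money, so its weight enters the valuation of home refills that the DCE is meant to supply. The wording is fixed in the protocol as content of the instrument, so it is not a detail that can be left to a statistical analysis plan.

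**Working it through.** The protocol states no step size or willingness-to-pay figure, so there is nothing to reproduce. The inputs are the three levels in Table 2.

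**Spacing of the levels.** Risk per 1,000 refills = 1,000 / denominator.

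| Displayed denominator | Risk per 1,000 | Step in denominator | Step in risk per 1,000 |
|---|---|---|---|
| 100 | 10 | – | – |
| 500 | 2 | 400 | 8 |
| 1,000 | 1 | 500 | 1 |

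- Ratio of the risk steps, large to small: 8 / 1 = 8.
- Ratio of the denominator steps, in the same order: 400 / 500 = 0.8.
- The middle level lies (500 − 100) / 900 = 44% of the way along the displayed scale. On the risk scale it lies (2 − 1) / 9 = 11% above the lowest risk.
- As risk ratios, the steps are 10 / 2 = 5 and 2 / 1 = 2.

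**Can the analysis repair a misreading?** This illustration uses assumptions that are not in the protocol: a cost coefficient of −0.02 per euro, a utility of 1.0 across the whole risk range, and 200,000 simulated choices fitted by conditional logit. Willingness-to-pay for a step is its utility divided by 0.02.

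- Patients respond to denominators: (400/900)/0.02 = 22.2 euros for 1 in 100 to 1 in 500, and (500/900)/0.02 = 27.8 euros for 1 in 500 to 1 in 1,000.
- Patients respond to true risk: (8/9)/0.02 = 44.4 euros and (1/9)/0.02 = 5.6 euros.

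| How patients respond | Values acted on (euros) | Categorical coding returns | Linear-in-risk coding returns |
|---|---|---|---|
| To denominators | 22.2 and 27.8 | 22.0 and 28.2 | 36.1 and 4.5 |
| To true risk | 44.4 and 5.6 | 44.3 and 5.0 | 44.0 and 5.5 |

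Categorical coding returns whatever patients acted on, misreading included. Linear coding imposes the risk scale and then fits badly if patients used the other one. If patients read the risks correctly, both codings do well. For the small step, the two ways of reading differ by 27.8 − 5.6 = 22.2 euros, on a cost attribute with levels 0, 40 and 70 euros. That figure depends wholly on the assumed coefficients. It shows what could happen and does not estimate what will.

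**The case against.** The strongest reply is that the plan contains no error. Tables 2 and 3 agree, each level is a correct statement of a risk, and unequal spacing of attribute levels is not a fault. Nothing in the documents shows that patients react to denominators; if they react to the risks, there is no distortion. The full survey is not shown and may contain explanations or a risk graphic. All of this stands, and it limits the point to a possible bias.

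Several stronger readings are tempting, and the documents do not support them.

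- *The format does distort willingness-to-pay.* This needs evidence of misreading, which the protocol neither gives nor excludes.
- *An eightfold error in the value of an infection avoided.* If both steps were valued at 40 euros, the implied values would be 40/0.008 = 5,000 and 40/0.001 = 40,000 euros per infection avoided. The factor of eight is simply the ratio of the steps, and equal valuation is assumed at the outset. It could also be a genuine preference, since the protocol does not say that patients should value risk linearly. Nor does the protocol set a target for willingness-to-pay per infection avoided.
- *The design works against home refills.* In Table 3 home carries the higher risk, by the small step, but that table is one example. Section 10.4.3 varies the attributes across scenarios.
- *English speakers will read 1.000 as one.* Section 5.1.5 does use the dot both as a decimal mark and as a thousands mark. After 100 and 500, though, most readers will infer one thousand, and the English survey is not shown. This is a minor matter of tidiness.

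What survives is that the format makes an 8:1 spacing hard to see, and that no later coding can tell a misreading from a preference.

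**Conclusion.** The point holds as a minor, inexpensive improvement to the instrument. The spacing follows directly from Table 2: risk steps of 8 and 1 per 1,000 behind displayed steps of 400 and 500. The consequence is conditional. If patients respond to the displayed numbers, the small step is overweighted relative to the large one, and the bias can pass into the willingness-to-pay for home refills. Its direction for that total depends on which risks are assigned to home and hospital in the valuation, which the protocol does not fix. Its size cannot be derived from the documents.

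The comparison of comfort between home and hospital, which is the primary outcome, is not touched. The DCE complements the cost-utility analysis and does not replace it.

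**What to change.** In Tables 2 and 3 and in every language version of the survey, show the three levels as *10 in 1000 refills*, *2 in 1000 refills* and *1 in 1000 refills*, with no thousands dot. The levels and the experimental design stay as they are. The 8:1 spacing remains; it becomes visible.

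The cost is a rewording of three labels. By the spacing of about 2–3 months between refills in section 10.4.3, a patient reaches the DCE three intervals, or about 6–9 months, after the first refill. An early change would therefore come before most answers, although the protocol gives no accrual figures to confirm this.

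The small downside concerns answers already given under the present labels. They need a sensitivity analysis, or an interaction of wording version with the risk levels. A main effect for wording version will not do: it takes the same value in both scenarios of a choice set and cancels. Such interactions would be imprecise, since the planned 82 patients less 20% loss leave 0.8 × 82 = about 66 completers.
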